Tobacco use is one of the main causes of preventable deaths worldwide. Tobacco use is associated with cardiovascular diseases. There are currently about one billion smokers in the world. An estimated six trillion cigarettes are smoked annually by current smokers. Six million people die each year from tobacco use and exposure (WHO, 2011a). The GHS (2017a) reported that the prevalence of tobacco use in Ghana in 2014 was 5.1% among males and 0.4% for females. A research conducted among students of 11-17 years in Ghana revealed that prevalence of smoking among boys was 2.4% while girl smokers was 1.4% (Mamudu & Veeranki, 2013).

Alcohol consumption is associated with the risk of hypertension and hemorrhagic stroke. Globally, an estimated 3.3 million people died (5.9% of all worldwide deaths) in 2012 as a result of alcohol consumption. More than half of these deaths resulted in NCDs of which CVDs and diabetes accounted for 33% of these deaths. Globally, the levels of alcohol consumption in 2010 was estimated at 6.2 liters of pure alcohol per person ≥15 years of age (WHO, 2014). In Ghana, the levels of alcohol consumption in 2016 per person ≥15 years of age was estimated to be 2.7 liters (WHO, 2018a). In a research among 1,311 adolescents school students in Ghana found that prevalence of alcohol use among students was 42.3% (Hormenu, Hagan, & Schack, 2018).

Unhealthy diet accounts for 1.7 million deaths and 16 million DALYs worldwide as a result of low consumption of fruits and vegetables (WHO, 2014). Adequate fruits and vegetables intake reduces the risk of CVDs (Boeing et al., 2012). Consumption of high energy foods including processed foods like fats and sugars results in obesity (Mendonca et al., 2016). Also, high salt intake increases the risk of hypertension and

CVDs. Globally, the WHO has estimated that people consume between 9-12 g/day of salt which is far above the recommended intake of less than 5g/day. The WHO further indicated that saturated fat predisposes an individual to the risk of coronary heart diseases whereas monounsaturated and polyunsaturated reduces the risk (WHO, 2011a) while the consumption of fish is very low. A study in Ghana among secondary school students revealed the consumption of sweet snacks, sodas, and energy dense foods were high (Amoh & Appiah-Brempong, 2017).

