**1.6 Research Hypotheses**

The research hypotheses of this study are:

1. There will be no difference in the socio-demographic characteristics between the intervention and control groups at baseline.

2. The behavioral modification intervention program will be effective in improving the knowledge of CVD and its risk factors, motivation, and behavioral skill score among the participants in the intervention group as compared to control group and also within the groups from baseline to six months among secondary school students in Brong Ahafo, Ghana.

3. The behavioral modification intervention program will be effective in promoting physical activity levels of participants in the intervention group as compared to control group and also within the groups from baseline to six months among secondary school students in Brong Ahafo, Ghana.

4. The behavioral modification intervention program will be effective in reducing the prevalence of smoking among participants in the intervention group as compared to control group and also within the groups from baseline to six months among secondary school students in Brong Ahafo, Ghana.

5. The behavioral modification intervention program will be effective in reducing the prevalence of alcohol consumption of participants in the intervention group as compared to control group and also within the groups from baseline to six months among secondary school students in Brong Ahafo, Ghana.

6. The behavioral modification intervention program will be effective in promoting fruits and vegetable intake among participants in the intervention group as compared to control group and also within the groups from baseline to six months among secondary school students in Brong Ahafo, Ghana.

7. The behavioral modification intervention program will be effective in increasing seafood and water intake and reducing carbohydrates, fats and oils, fried eggs, fried chicken, carbonated drinks, plain sugar, sweet snack, and salted fish intake among participants in the intervention group compared to control group and also within the groups from baseline to six months among secondary school students in Brong Ahafo, Ghana.

8. The behavioral modification intervention program will be effective in reducing body weight and BMI of participants in the intervention group as compared to control group and also within the groups from baseline to six months among secondary school students in Brong Ahafo, Ghana.

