Furthermore, some school-based RCT intervention studies on smoking have been successful whereas some had not. An RCT by Hiemstra et al. (2014) was conducted among elementary school children between the ages of 9-11 years. A total of 1478 students from 418 schools participated in the trial alongside their parents. An independent statistician randomized schools into intervention (728) and control (750) arms of the study and were followed for three years. The intervention, smoke free kids, concentrated on the prevention of smoking activities in families in order to prevent kids from smoking. The intervention module consisted of educational materials on smoking prevention that were sent to mothers via email. At the end of the study,

10.8% of the children in the intervention started smoking as compared to 12% in the control and there was no significance difference between the intervention and the control groups (odds ratio = 0.90, 95% CI, 0.63-1.27).

A randomized controlled trial was carried out to reduce the risk of smoking and alcohol use in a school setting among sixth graders. The intervention called ‘’unplugged’’ was delivered by trained teachers which focused on knowledge, attitudes, interpersonal skills, and intrapersonal skills over 45 minutes for a period of 12 months. The primary outcome was cigarette smoking patterns. Baseline and follow up data were taken at 1, 3, 12, 15, and 24 months with a total of 1874 students, and at

the final follow up students’ numbers dropped to 1753. The control on the other hand did not receive the intervention. However, there was a statistically significant effect for the final follow up for smoking and alcohol between the intervention and the control arm (Gabrhelik et al., 2012).

A school based intervention program Isensee et al. (2014) was carried out for 5th and

6th graders with the aim to prevent substance use. The intervention was delivered through life skills and that of specific skills which was tailored through substance abuse. This included coping with stress, problems, emotions, pressures to smoke and take alcohol. A total of 3444 from 45 schools took the baseline survey and 2513 (73%) took part in the post-intervention analysis. The prevention program was delivered in

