**3.6 Sample Size Estimation**

The minimum sample size required to test the study hypotheses was calculated using the two proportions formula (Lemeshow, Hosmer, Klar, & Lwanga, 1990). The formula gave the required number (n) for each group.

2

{√2p̌ (1 − p̌) + Z1−β√p1(1 − p1) + p2(1 − p2)}

n =

(p1 − p2)2

Parameters from different intervention studies were substituted into the formula to calculate sample size as shown in Appendix H. However, a study among students by Mohammed et al. (2016) was adopted to calculate the sample size for this study.

P1 = 0.032 (proportion of students who initiated smoking among students in the intervention group after six months intervention.

P2 = 0.088 (proportion of students who initiated smoking among students in the control group after six months.

P = proportion of all subjects receiving smoking intervention after six months ((P1 +

P2)/2).

P = (0.032 + 0.088)/2 = 0.06

With Z1-α/2 = 1.96 at 95% CI and Z1-β = 1.28, at 90% power gave a minimum sample

size (n0) of 281

Adjustments were made for estimated response rates (Aday & Cornelius, 2006) thus:

i) Adjustment for estimated response rate, where the estimated attrition rate

is 20% = 337.2

This gave a sample size of 337.2 students in each group. Cluster randomized control trials are measured by design effect given as (1+ (M-1) X ICC) = 1.085.

ICC – Intra Cluster Correlation = 0.01

M – Average Cluster Size

337.2 x 1.085 (effect size of cluster random sampling) = 365.9

This gave a sample size of 366 students per group, which was then multiplied by two since the study is in two arms. Therefore, 732 is the sample required for this study.

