**3.17.3 Inferential Statistics**

Chi-square tests will be performed to compare baseline characteristics of groups by their socio-demographic factors, family factors, CVD knowledge, motivation, behavioral skills, physical activity, smoking status, alcohol intake, BMI, systolic and diastolic BP. Independent t-tests will be performed to determine the between groups differences of total knowledge, motivation, behavioral skills, physical activities, dietary intake, BMI, diastolic and systolic BP. At six months post intervention, the independent and paired sample t-tests would be performed to determine the between and within group differences of variables respectively. Chi-square and the McNemar tests will also be performed on smoking status and alcohol intake at six months to determine the difference between and within groups since the variables are categorical variables.

A mixed design repeated measures analysis of variance (ANOVA) will be performed after checking that there is no substantial non-normality of residuals to determine the between and within group differences and its interactions on time differences on CVD knowledge, motivation, behavioral skills, physical activity, dietary intake, body weight, BMI, diastolic and systolic BP. Intention-to- treat (ITT) analysis will be the method that will be used to handle missing data in the analysis. Replacement of data will then be conducted for each missing variable using the multiple imputation method, following which Generalized Linear Mixed Model (GLMM) analysis will be performed to determine the overall effectiveness of the intervention study.

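### Hypothesis 4 counts a within-group fall in smoking prevalence as evidence of effectiveness, but the trial is planned on preventing initiation, so a programme that works as planned can show no fall, or a rise, in its own arm

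*Protocol*

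**What the plan says.** - **Hypothesis and objective.** Hypothesis 4 (Protocol 1.6) describes the programme as "effective in reducing the prevalence of smoking among participants in the intervention group as compared to control group and also within the groups"; the change is measured over the six months of the trial. Objective 5 (1.5.2) sets the same two-part aim for CVD risk factors generally, smoking included.
- **Test.** Section 3.17.3: "Chi-square and the McNemar tests will also be performed on smoking status and alcohol intake at six months". Chi-square serves the between-group comparison and McNemar the within-group one. The same section leaves overall effectiveness to a GLMM, and the abstract says that this model tests group, time and their interaction.
- **Planning figures.** Section 3.6 uses initiation, not prevalence. For the intervention arm it gives "P1 = 0.032 (proportion of students who initiated smoking among students in the intervention group after six months intervention"; the matching entry for the other arm is "P2 = 0.088 (proportion of students who initiated smoking among students in the control group after six months". It gives no baseline prevalence and no quit rate.
- **Background prevalence.** Section 1.1 cites a survey of Ghanaian students aged 11 to 17: "prevalence of smoking among boys was 2.4% while girl smokers was 1.4" per cent. Section 2.6.2 also cites 9% in Chinese secondary students and 10% for Ghana overall.
- **Literature.** Section 2.6.2 reports another prevention trial in which "10.8% of the children in the intervention started smoking as compared to 12% in the control". This result plays no part in the sample size.
- **Definitions.** Section 3.16.4 separates never smokers, current smokers, and those who tried and stopped. Hypothesis 4 does not say which of these defines prevalence.
- **Content.** The module (Tables 3.1 and 3.4) covers both quitting and not starting.

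**The concern.** The quantity that the trial is planned to change and the quantity that hypothesis 4 says will change are different. The programme does what 3.6 plans if fewer students start smoking than in the control schools. The within-group part of hypothesis 4 is met only if smokers are lost on balance over six months. Without a planned quit rate, nothing in the protocol links the two.

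Smoking is a primary outcome (3.15.2) and the basis of the sample size. A programme that cuts initiation from 8.8% to 3.2%, a relative reduction of (0.088 − 0.032)/0.088 = 64%, could be reported as not supporting part of hypothesis 4, or as followed by a significant rise in smoking. The within-group test also has no comparator. It mixes the programme effect with the ordinary take-up of smoking as students age, which only the randomised contrast can separate.

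**Working it through.** **The plan's own figure.** With P1 = 0.032, P2 = 0.088 and mean 0.06, the two-proportion formula with z = 1.96 and 1.28 gives 375.5 per group; with z = 0.84 it gives 280.8. The stated 281 is therefore the 80% power figure, although 3.6 says "With Z1-α/2 = 1.96 at 95% CI and Z1-β = 1.28, at 90% power gave a minimum sample" size of 281. That is a separate matter. The check below uses only P1, P2 and the 424 students per arm in 3.11.

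**Ever-smoking.** A student who has tried smoking cannot become a never smoker. With 3.2% initiation among baseline never smokers, ever-smoking can only rise.

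**Current smoking.** Let b be baseline prevalence, q the share of baseline smokers who quit, and s the share of starters still smoking at six months. The protocol fixes none of these for planning; q and s are assumptions and are varied here.

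- Prevalence at six months = b(1 − q) + 0.032·s·(1 − b)
- Break-even quit share = 0.032·s·(1 − b)/b

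| b | source | s | none quit | half quit | all quit | a fall needs q above |
|---|---|---|---|---|---|---|
| 1.4% | 1.1, girls | 1 | 4.6% | 3.9% | 3.2% | not possible |
| 2.4% | 1.1, boys | 1 | 5.5% | 4.3% | 3.1% | not possible |
| 2.4% | 1.1, boys | 0.5 | 4.0% | 2.8% | 1.6% | 65% |
| 5% | assumed | 1 | 8.0% | 5.5% | 3.0% | 61% |
| 10% | 2.6.2, Ghana overall | 1 | 12.9% | 7.9% | 2.9% | 29% |

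With s = 1, a fall is arithmetically possible only if b exceeds 0.032/1.032 = 3.1%.

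**In students.** At b = 2.4% and s = 1, the intervention arm expects 424 × 0.976 × 0.032 = 13.2 starters and at most 424 × 0.024 = 10.2 quitters.

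**What McNemar would show.** Simulated exact McNemar test, two-sided 5%, intervention arm, students treated as independent:

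| b | s | n | q | significant fall | significant rise |
|---|---|---|---|---|---|
| 2.4% | 1 | 424 | 100% | about 0.25% | 6% |
| 2.4% | 1 | 424 | 50% | 0% | 40% |
| 2.4% | 1 | 424 | 20% | 0% | 81% |
| 2.4% | 1 | 339 (20% attrition) | 50% | about 0% | 31% |
| 2.4% | 1 | 339 (20% attrition) | 20% | 0% | 68% |
| 2.4% | 0.5 | 424 | 50% | below 1% | about 3% |
| 2.4% | 0.5 | 424 | 20% | 0% | 22% |
| 10% | 1 | 424 | 50% | 28% | 0% |

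**The between-arm contrast in the same scenario.** At b = 2.4%, s = 1 and half quitting in both arms, the intervention arm ends at 0.012 + 0.032 × 0.976 = 4.3% and control at 0.012 + 0.088 × 0.976 = 9.8%. Both arms rise, yet the intervention is ahead by 5.5 points.

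**The case against.** - **The planning figures do not force a rise.** A reader might infer that the protocol's own numbers make current smoking go up whatever happens. They do not. Section 3.6 fixes only initiation. The 1.4% to 2.4% is a background survey figure for ages 11 to 17, while the trial's students are 14 to 19. At a higher baseline with enough quitting, prevalence falls. This stands.
- **Starters need not still be smoking.** The questionnaire asks separately about ever trying a cigarette, even a puff or two, and about still smoking. If half of starters have stopped, the chance of a significant rise drops from 40% to about 3% (half quit) and from 81% to 22% (20% quit). This stands, and it limits the size of the point.
- **Cessation is a stated aim of the module.** A fall in current smoking is therefore a coherent goal. True, but the protocol plans no quit rate, so it gives no ground for expecting quitters to outnumber continuing starters.
- **No pass/fail rule exists.** A reader might infer that a successful programme must formally fail hypothesis 4. The documents do not support that. The same clause recurs in hypotheses 2 to 9, read literally it covers the control group too, and 3.17.3 gives overall effectiveness to the GLMM. What remains is that objective 5 and hypothesis 4 still present the within-group fall as part of effectiveness.
- **The trial cited in 2.6.2 is no planning input.** It was home-based, in children aged 9 to 11, with three years of follow-up and no significant difference. It illustrates initiation in both arms and nothing more.

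**Conclusion.** The point holds in a limited form. Objective 5 and hypothesis 4 treat a within-group fall in smoking prevalence as evidence of effectiveness, while 3.6 plans on initiation. The two agree only if quitters outnumber starters who still smoke, which the protocol nowhere assumes.

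If prevalence means ever-smoking, the within-group part cannot be met. If it means current smoking, the result depends on three quantities left open: baseline prevalence, quitting, and how many starters persist. At the cited 1.4% to 2.4% with all starters persisting, prevalence rises even with complete quitting. Otherwise a fall needs substantial quitting: about 65% from 2.4% if half of starters persist, and about 61% or 29% from 5% or 10% if all do. The simulated test results rest on the same assumptions and ignore clustering by school.

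Only the within-group part is affected. The between-arm part agrees with the planning figures and favours the intervention whenever they hold and quitting is similar in the two arms. In every scenario the within-group test cannot separate programme effect from time trend.

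**What to change.** 1. In 1.6, delete the within-group, baseline-to-six-months clause from hypothesis 4. In 1.5.2, remove the matching clause of objective 5 as it applies to smoking.
2. In 1.6 or 3.16.4, state which smoking category defines prevalence.
3. In 3.17.3, report McNemar for smoking in both arms as description only, or not at all.
4. In 3.17.3, state that effectiveness on smoking is judged by the between-arm contrast from the planned GLMM: group by time, using baseline smoking status and accounting for school. A bare six-month comparison would discard the baseline information that the plan already collects.
5. Tabulate by arm the starters among baseline never smokers and the quitters among baseline smokers. This shows prevention and cessation separately.

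The cost is wording only; the questionnaire already collects what is needed. The within-group p-values for smoking, in both arms, would no longer count as evidence of effect.

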**2.6.3 Alcohol Consumption**

**2.6.3.1 Culture of Alcohol Consumption in Ghana**

In Ghanaian societies, alcohol is mainly consumed by adults, while the youth are not allowed to take alcohol. Excess drinking and intoxication is generally viewed with extreme disapproval. The patterns of alcohol consumption are however reported to have changed due to sociocultural changes and the growth of alcohol industries and the youth have taken to drinking of alcohol. The type of alcoholic beverage consumed in many of the societies in Ghana include locally produced home brewed beverages with very high alcohol content and increased health and social consequences such as “akpeteshie” (WHO, 2018b; GSS, 2012).

Cultural background of the students may also play a role as they may have been exposed to alcohol consumption from their cultural backgrounds. Most cultures in Ghana use alcohol frequently for many functions (such as naming ceremonies) and students are exposed to these practices and tend to carry it on as a practice of their own. Advertisement of alcoholic drinks is also seen to play a major role in the consumption of alcohol by students. The alcohol producing companies win customers through attractive branding, persuasive advertisement and promotion. The alcoholic beverages are made to suit the demands of customers and these are also mentioned in advertisements to reinforce the interest of consumers (WHO, 2018b; Oppong Asante, Meyer-Weitz, & Petersen, 2014; Bosu, 2010).

Although alcohol are not supposed to be sold to children in Ghana like many other countries, but more often than not they get sold to children regardless of the policies in place. The reasons associated to alcohol use by children is mainly due to peer pressure (Elisaus et al., 2015) and the lack of knowledge of the harmful effects of alcohol amongst others. Therefore, one of the surest ways used in this study was to do primary prevention with the use of the IMB model to educate the intervention group on the dangers associated with alcohol and to encourage, and give some behavioral skills to stop or not to initiate alcohol.

**2.6.3.2 Previous School Based Study on Alcohol Consumption**

Harmful intake of alcohol alone caused 2.3 million deaths worldwide in 2003 which accounted for 3.8% deaths worldwide (WHO, 2011b) and the deaths rose to 3.3 million in 2012 (WHO, 2014). There is a direct relationship between high alcohol consumption and cardiovascular diseases (Holmes et al., 2014; Shakeshaft et al., 2014). According to Movva and Figueredo (2013), consumption of alcohol caused cardiac arrhythmias, cardiomyopathy, and hemorrhagic stroke. Ikehara et al. (2013) reported in their prospective study of 47,000 Japanese women that alcohol drinking was associated with high risk of stroke. Also, use of alcohol increases risk of hypertension (Briasoulis, Agarwal, & Messerli, 2012) which is a single risk factor for CVD.

In Ghana, total alcohol consumption per capita in 2010 was 4.8 liters; with males consuming 7.8 liters and 1.9 liters for females (WHO, 2015c). Further, 5.1% DALYs of the global burden of disease is attributed to alcohol consumption. A study conducted among 227 Ghanaians of age 8 years and older reported that 12% of the children take alcohol daily (Oppong Asante et al., 2014). In another survey conducted in Ghana among school going age adolescents revealed that the prevalence of current alcohol use was 12.6% (Oppong Asante & Kugbey, 2019).

School-based randomized control trials have been undertaken to reduce alcohol intake among students. An RCT trial was carried out to evaluate the effectiveness of a school- based alcohol harm prevention intervention among students between the ages of 13-

14 years for a period of nine months. A total of 21 schools (1746) participated in the trial which was made up of 14 schools (1161) in the intervention with 7 schools (585) in the control arm. Students in the intervention group received comprehensive focused drug minimization education which was conducted by teachers while the control group carried on with their normal drug education programme taught by schools. The main outcome was general knowledge of drug and alcohol consumption. There was a statistically significant increase in knowledge about drugs and alcohol (*p* < 0.001) among students in the intervention group as compared to the control group. There was no significant differences between the two groups in terms of alcohol consumption (Midford et al., 2014).

A meta-analysis of randomized control trials on effectiveness of school-based preventive interventions on students alcohol use was carried out by Strøm et al. (2014) of articles published from January 1990 to August 2015. A total of 28 (39289) randomized control trials studies were used in the meta-analysis. The researchers reported in their findings that the overall effect size was small but was positive among studies with the frequency and quantity of alcohol. There was however no effect found among studies that measured proportion of alcohol use.

Another cluster randomized control trial with two arms was conducted to prevent alcohol use among secondary school students. Students from 15 schools with ages from 13-15 years participated in the trial where seven schools with 343 students and eight schools with 356 students were randomly allocated into the intervention and control arms of the study respectively. The intervention consisted of a two 90 minute sessions for two weeks during school hours which consisted mainly on education in avoiding behaviors that led to alcohol consumption. The intervention education was carried out by three qualified counsellors and two facilitators. Students in the control arm received no intervention and went on with their normal school lessons. The main outcome measurement of the study was consumption of large quantities of alcohol at

12 months. The findings showed no statistically significant difference between rates of consumption in the intervention, 42.9%, and control, 49.2%, groups at 12 months follow up (Lammers et al., 2015).

Tripodi et al. (2010) conducted a meta-analytic review to assess the effectiveness of substance abuse interventions among students between the ages of 12-19 years to reduce alcohol intake. A total of 16 studies were used in the analysis. Frequency of alcohol use, quantity of alcohol use and abstinence were measured after post intervention between one month and a year in the study. The findings showed that interventions significantly reduced alcohol intake among the adolescents with a pooled effect of −0.61 (95% CI, −0.83 to −0.40 *p <* 0.001).

